### Recruitment of participants

Patients will be identified through review of the vasculitis and renal registry lists held by the renal team at Royal Preston Hospital. Patients aged over 18 years old, receiving or previously received immunosuppressive therapy for a diagnosis of AAV in keeping with the Chapel Hill Consensus Criteria [26] will be included. Patients with active and relapsing disease as well as those in remission will be recruited. Research methodologies will involve completing questionnaires and semi-structured interviews; therefore, a good level of English literacy will be an inclusion criterion. Exclusion criteria will include patients who do not meet Chapel Hill Consensus criteria for AAV, those who are unable to consent and those who have dual positivity with anti-glomerular basement membrane antibodies or any other autoimmune condition that is active or being actively treated.

### Consent and ground rules

Written consent will be gained for all participants and it will be made clear that they can withdraw from the study at any time until the point data analysis has commenced when it will not be possible to extract their data. Quotes from the focus groups may be used anonymously in publications or to support the study analysis and conclusions, and this will be agreed with all consenting participants. All data and information documented will be confidential. Due to the nature of the group settings, participants will be asked to maintain confidentiality and respect the privacy of others. Participants will be asked not to disclose any matters discussed to anyone else and adhere to the ground rules set out as part of the sessions. The ground rules will be presented to ensure all participants can be involved equally and ensure the session runs to plan.

### Focus groups

Up to three focus groups will be held to achieve a total of 15–20 patient participants. Focus groups will be 2.5 hours long with a comfort break and time for refreshments built in. Each session will contain 5–8 participants to limit side conversations and allow equal opportunity to contribute and present their views. The location of the focus groups will be outside the clinical setting in a central location with easy access for all disabilities. Sessions will be audio recorded for transcription purposes. The option of a virtual meeting will be explored in the event that the COVID-19 pandemic impacts on the ability to safely conduct face to face sessions.

The sessions will be facilitated by a minimum of 2 but ideally 3 moderators, as advised by Krueger *et al*. [27] guidance in conducting focus groups. The main moderator will be responsible for introductions, addressing and implementing ground rules, introducing topics for discussion, facilitating the discussion, using prompts and encouraging all members to participate. Co-moderators will be responsible for the recording of the session, taking field notes, sorting refreshments, supporting those that require some time out of the session or who may be running late for example and helping the moderator keep to time.

### Topic guide

A semi-structured topic guide will be developed with influence from the existing literature to gain a comprehensive understanding of the lived experiences of each participant. Four broad areas of interest have been created to address 1) the effects of AAV on everyday life and living, 2) the effects of treatment on everyday life and living, 3) the role of patients in health management and the patient experience 4) a review of the existing PROM tools. Using guidance from Morse and Field [28] the interview structure follows thematically on from each theme and aims to introduce only one aspect of a topic at a time.

Different types of question style will be used throughout the session to focus the group discussion. Open questions will be used to introduce and facilitate discussion at the start of each of the topics that are introduced. Exploration questions will be used throughout the session as generic prompts so as to engage the whole group. Phases such as ‘is that experience similar for all of you?’, ‘does anyone have anything else to add to that point?’ and ‘does anyone have a different experience / thoughts about that?’ can be used to facilitate this. Specific questions and closed questioning may be used to facilitate and probe at more specific details, reflections or perspectives in key areas. Exit questions will be used at the end to ensure all topics have been covered and to ensure ongoing engagement. Examples could be ‘Is there anything else that you would like to add?’.

### Ethics

This study is to be conducted according to European Union and international standards of Good Clinical Practice. Informed written consent will be gained for all participants. Participants will be reminded to maintain confidentiality and respect privacy, although guaranteeing confidentiality of discussed topics cannot be ensured from patient participants. Sensitive topics may arise organically with the potential to cause emotional distress. The supportive group environment and moderator team will handle these topics sensitively, offering breaks and reminding participants of their right to withdraw. Mandatory contribution is not required, and the schedule prevents lengthy and detailed responses, minimising distress.

### Reflexivity

As part of the methodology of this qualitative study researchers will be encouraged to engage with reflexivity. Whilst different definitions of reflexivity exist, most describe it as the researcher’s ability to ‘examine how they and the intersubjective elements that exist influence and transform research topics’ [29, 30]. This reflective practice is integral to ensuring quality control of the data collection and analysis so as to consider how the researchers own experiences and assumptions influence aspects of the study. Reflective practices that explore personal, interpersonal, methodological and contextual reflexivity will be included. The value of this is to consider how the researcher engages with the data and how their perspective and expectations can influence and inform the research questions and outcomes.

## Results

### Transcription and analysis

The audio transcript of each focus group will be listened to and transcribed verbatim by lead researcher LF. Data will be analysed using a combination of inductive and deductive framework analysis [31]. The recorded audio and transcript data will be reviewed several times to ensure a thorough understanding of the content is obtained as well as initial indexing of key words and concepts and preliminary notes will be made. Working through the transcripts as well as additional notes from the moderators, constant comparisons will be made and initial observations will be further developed into ‘clusters’ of information called ‘codes’ based on similarity. Codes will then be assessed and grouped into themes which capture a greater interpreted meaning.

*A*-priori codes and themes will be informed deductively from findings of a previous systematic review and applied to focus group data as appropriate. Codes and themes grounded in the data will be created inductively and used to enhance deductive themes. NVivo [32] will be used to analyse the data and for qualitative data management although some pen and paper methods may be applied depending on consensus from the research team. Mapping of connections between categories will be used especially in relation to treatment or organ specific themes, so as to explore any relationships and to define a multi-dimensional theoretical construct of HRQoL for this patient group [31]. Throughout the process there will be back and forth between the transcript and analysis to ensure a full capture of the data and accurate representation of themes. Following full analysis, the key themes that emerged will be presented from the qualitative work. The themes arising from the framework analysis will be assessed by members of the research team and 2–3 patient participants and used to inform the questions included in a new PROMs tool. Wording and overall relevance will be explored to ensure the tool is fully relevant and representative.

For analysis and validation of Phase II, quantitative data will be analysed using statistical analysis software. Analysis will include descriptive statistics and inferential statistics. Descriptive statistics (means, standard deviations, percentages) will be used to explore the data for acceptability due to missing data (<10%) and floor to ceiling effects (no item endorsed by >80% at the extreme response anchors). Correlational techniques such as Pearson’s correlation co-efficients, inter-class and intra-class correlations, Cronbach’s alpha, and factor analysis, will be used to determine validity (discriminant, construct and criterion), reliability and factor structure.

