The 29-item AAV-PRO is the only disease specific tool currently available for the use in AAV and includes domains relating to systemic and organ specific symptoms, treatment related side effects, psychological and social well-being, impact on physical function and concerns about the future [6, 16]. The tool has been validated globally and translated into many different languages. It has demonstrated good face and construct validity and reliability [16, 17]. However, as with any tool there are recognised limitations, such as its ability to measure and assess changes over time. The 4-week assessment period has the potential to under report both transient and chronic symptoms, whilst limited facets address the economic impact on HRQoL. Furthermore, the tool was designed for application in clinical research and trials and its usability or suitability for real-time use in routine, clinical practice may be limited.

This study has been designed to better recognise the gap that exists in evidencing and understanding the key factors that are important to patients living with AAV. We aim to develop a tool that can be used in clinical practice to help aid patient and clinicians understanding and track changes in HRQoL over time. At an individual level, better understanding of the disease burden may facilitate a holistic, patient-centred approach to clinical decision making and identify those patients at risk or vulnerable to treatment related toxicities or relapsing disease. On a wider and longer-term level, these outcomes can be used to compare treatments, provide insight into inequalities, inform care pathways and allow for service enhancements (Fig 1). Here we present a protocol for this exploratory qualitative study which includes details on the methodology, data analysis and ways in which we aim to improve PROs and HRQoL as a result.

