**Phase II.** Is the application and validation of the PROMs tool. In order to fully complete psychometric evaluations, other data including clinical data from medical records and treatment information may be needed to fully correlate with the PROMs tool. Which other data we collect will be determined by what is established from Phase I where we establish what patient’s value most when considering HRQoL. The protocol estimates a sample size of 200–250 participants to ensure adequate statistical power, following the established principle of 10 people per item included assuming a maximum of 20–25 items included in the final version [25].

The newly developed PROM will be sent to patients either by email or given during routine clinic appointments. The tool will be a pen and paper survey which is self-completed by patients. There will be deposit boxes in clinic or the option of email return of scanned copies (including photos taken using smart phone technology or similar) and patients will be encouraged to discuss their outcomes with healthcare professionals in clinic if they wish to. Statistical analyses will be used to assess the psychometric properties of the tool and test the structure of the questionnaire. Psychometric properties will include: construct validity, criterion validity, floor and ceiling effects, sensitivity to change and internal construct reliability. A test- retest analysis will be carried out 1 month following the initial questionnaire. The initial questionnaire will have an option box asking if patients are happy to be contacted again for further follow up questions. Of those that agree by ticking this box, a sub sample (n = 100) of randomly selected participants will be identified and asked to complete the test survey again with a specific yes / no question asking if anything substantial had changed in relation to their illness or treatment.

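### The only stated floor/ceiling criterion is a per-item limit of 80%, which could pass short domain scores on which about half of patients cannot register change in one direction

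*Protocol article*

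**What the plan says.** The Phase II description in the protocol article (Study setting and design) says that "Statistical analyses will be used to assess the psychometric properties of the tool and test the structure of the questionnaire". The properties it names are "construct validity, criterion validity, floor and ceiling effects, sensitivity to change and internal construct reliability", with no criterion attached to any of them there.

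The number comes later, in the Phase II paragraph of Transcription and analysis. Descriptive statistics are to be used to look at acceptability under two limits, one for missing data (below 10%) and one for "floor to ceiling effects (no item endorsed by >80% at the extreme response anchors". This second limit is the only floor/ceiling criterion in the article, and its unit is the item.

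Three other statements bear on it:

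- The Introduction says the tool should help to "track changes in HRQoL over time". The aims section adds that relapse and remission are to be taken into account.
- Recruitment of participants says that "Patients with active and relapsing disease as well as those in remission will be recruited".
- The size of Phase II is 200–250, from "10 people per item included assuming a maximum of 20–25 items included in the final version".

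**The concern.** A floor or ceiling effect matters because a patient at the end of the scale cannot be seen to move beyond it. For a tool meant to follow patients over time, the check should show how much room is left in whatever score is followed. The stated criterion looks only at items and tolerates four patients in five at one end.

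A per-item limit does not translate into a known limit for a sum of items. How many patients sit at the extreme of a domain depends on how many items it has and how strongly they correlate. With few items and moderate to high correlation, every item can pass while about half the sample has the lowest or highest possible domain score. A report that followed the criterion literally could then record no floor or ceiling problem for a domain with little room to show change in one direction.

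**Working it through.** **Inputs from the article.** Item limit: fails only above 80% (Transcription and analysis). Sample size 200–250, at 10 people per item and 20–25 items (Study setting and design, Phase II).

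**Assumptions, not in the article.** Inter-item correlation ρ, taken as 0.4–0.7 and also shown outside that range. A five-item domain as an example of a short one. All items at 79% or 80% at the same end of the scale. One-factor normal latent model with equal correlations.

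**Step 1: the plan's own figure.** 10 × 20 = 200 and 10 × 25 = 250, so the stated sample size is reproduced. The 80% limit is a chosen threshold with no derivation to check.

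**Step 2: what one item may look like and pass.** Largest passing count = 0.80 × N:

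- N = 200: 160 at the anchor, 40 with room to move further that way.
- N = 250: 200 at the anchor, 50 with room.

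The probability that an item passes is P(X ≤ 0.80 N), with X binomial (N, p):

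- true p = 0.70: 0.9995 (N = 200) and 0.9999 (N = 250).
- true p = 0.75: 0.96 (N = 200) and 0.97 (N = 250).

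So an item with 70–75% of patients at one anchor is rarely flagged.

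**Step 3: from items to scores.** A patient has the extreme score only if at the anchor on all k items. With item share p and c = Φ⁻¹(p),

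share at extreme = ∫ φ(x) · [Φ((c − √ρ·x)/√(1 − ρ))]^k dx.

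This becomes p^k at ρ = 0 (for example 0.80⁵ = 0.328) and p at ρ = 1.

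| Score | p | ρ = 0 | ρ = 0.4 | ρ = 0.5 | ρ = 0.7 | ρ = 0.8 |
|---|---|---|---|---|---|---|
| 5 items | 0.79 | 30.8% | 45.9% | 49.6% | 57.5% | 62.0% |
| 5 items | 0.80 | 32.8% | 47.6% | 51.2% | 59.0% | 63.4% |
| 20 items | 0.79 | 0.9% | 19.8% | 26.1% | 40.4% | 48.8% |
| 20 items | 0.80 | 1.2% | 21.1% | 27.6% | 42.0% | 50.3% |
| 25 items | 0.79 | 0.3% | 16.8% | 23.2% | 38.1% | 46.9% |
| 25 items | 0.80 | 0.4% | 18.0% | 24.6% | 39.6% | 48.4% |

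Over ρ = 0.4–0.7 the five-item domain runs from about 46% to 59%, and the 20–25 item total from about 17% to 42%. A majority at the extreme needs ρ of about 0.5 for the five-item domain, and about 0.8 or more for the total score.

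**Step 4: less extreme items.** With items at 50% and ρ = 0.5, 16.7% are at the extreme of a five-item domain and 4.8% at the extreme of a 20-item total. The exposure is greatest for short domains whose items lie near the permitted limit.

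**The case against.** The article is a condensed account, no analysis plan is shown, and domains will not exist until Phase I and the factor analysis are done. Silence about scores would therefore be no finding. That is correct. The point rests instead on the criterion that is printed: it is numeric, it is per item, and it does not bound what happens to a score.

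A reader might infer that a tool unable to show improvement in most patients would pass validation. The documents do not support this, for four reasons:

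- For a total of 20–25 items, a majority at the extreme requires every item near the limit and a correlation of about 0.8 or more.
- The criterion covers both ends of the scale. Only a pile-up at the best-health end blocks improvement; at the worst-health end it blocks deterioration.
- The threshold is one acceptability check. Sensitivity to change is listed as a separate property, although no criterion is given for it and the only repeat measurement described is a one-month test-retest in 100 participants.
- The article describes no scoring, so the use of domain scores in clinic is a reasonable expectation and not a stated fact.

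A lenient item limit also has a good argument behind it. AAV is a multi-organ disease and patients in remission are recruited, so many may truly have no problem on an organ-specific item. Such items can still register a relapse. This stands. It is why the 80% limit can remain for items, and why a tighter item-level review (for example at 50%) is a trade-off and not a requirement.

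**Conclusion.** The point holds in a limited form. The one stated floor/ceiling criterion is per item, and an item with up to 80% of patients at an anchor passes. Used alone, it could pass short domain scores on which a large share of patients cannot register change in one direction: about 46–59% for five items, and about 17–42% for a 20–25 item total.

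These ranges describe what the rule permits and do not forecast what will be observed. Weaker correlation, fewer items near the limit, or pile-ups at opposite ends of the scale would all lower them. What could change is the conclusion drawn about floor and ceiling effects in a tool intended to follow patients over time. The item check is worth supplementing, and nothing here shows that the tool itself would be unfit.

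**What to change.** Keep the 80% rule as an item-level screen. Add to the Phase II analysis that floor and ceiling effects will also be assessed on every domain score and on any total score. Report the share of respondents at the minimum and at the maximum separately, overall and by disease activity (active or relapsing disease, and remission), because the two ends limit different directions of change.

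Set the limit before Phase II data are seen. A figure of 15% at either end would serve as an example; it is a reviewer's proposal, not a figure from the documents, and the investigators may justify another. Say what follows when a score exceeds it, such as revising the domain or keeping it with a documented reason.

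The cost is about one sentence in the plan and one frequency table, with no new data beyond recording disease activity at completion if that is not already intended. The downside is that some domains may be flagged, and those covering rare but important problems will need a written reason to stay.

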### Data storage and management

Personal data held on an NHS computer will have appropriate access controls in place, limiting access to authorised individuals where it is required for the initial stages of study during participant identification and recruitment. All patient information, transcription and study data will be stored in password protected files in an access restricted network on a secure computer server within the Lancashire NHS Foundation Trust. Subsequent to this, only the direct research team will have access to anonymised data. The audio recording of the focus groups will be kept for a maximum of six months to allow for transcription and cross checking any queries before being deleted. Quotes from the focus groups may be used anonymously in publications or to support the study analysis and conclusions. All consent forms will be signed and photocopied twice. The consent forms will be labelled 1; Site file (Original), 2; participant copy, 3; medical records.

### Dissemination of results

At the end of the study period all appropriate results and findings will be fed back to participants. The format in which the findings are fed back will be determined with the patients, as to how they would like to receive it. Options include a written summary or short video presentation summarising the results. Results and study findings will be disseminated through peer reviewed scientific journals, conference presentations and internal reports. The 21 items set out in the standards for reporting qualitative research (SRQR) [33] will be met to ensure transparency and high standards of the study.

## Discussion

The outlined protocol aims to develop a disease-specific PROM for patients living with AAV that can be used in the routine clinical practice. Over recent decades there has been a shift in the way patients engage with healthcare and approaches such as shared decision making and self-management are more ubiquitous, especially amongst chronic disease groups. As it currently stands there is no ‘gold standard’ assessment of HRQoL in patients with AAV but its increasingly recognised that methods and strategies to measure and observe the key issues that are important to patients are needed. AAV is a multi-organ disease and the impact of the disease and its treatment may not always be externally visible or apparent. As such, a better understanding of how patients perceive their illness and its effects is crucial.

The majority of previously published studies available have used the SF-36 as a generic PROM tool and few other validated tools have been applied in the vasculitis cohort. Where disease specific tools such as the AAV-PRO has shown significant advancement over the SF-36, the use has been largely limited to clinical research. The Outcome Measures in Rheumatology (OMERACT) Vasculitis Working Group have endorsed the need for PROs and HRQoL assessments in clinical trials and recommend the use of the AAV-PRO [13, 17, 34, 35]. However when considering vasculitis trials, many participants have active or relapsing disease, which contrasts the primarily stable and inactive disease group from which the AAV-PRO was originally and subsequently validated [16, 36]. It has however been shown to correlate with patients self-reporting active disease and has strong psychometric properties compared to other outcome measurement tools [17, 36].

Disease specific PROMs designed for rare and chronic conditions have additional challenges such as the small patient populations, heterogenous conditions and limited literature [37]. It is therefore important that such tools are focused on being applicable and responsive. Whilst disease specific measures can provide more accurate representation of disease burden and specific symptoms compared to generic tools, they tend to be time consuming and cumbersome in clinical use [4, 38]. Historically questionnaires and tools had to be quick and easy to complete due to time pressures in a clinical setting, it is now recognised that it is not the time required that is most important to patients, but instead how meaningful patients feels the questions are and how much they relate to them. Furthermore, technology in the form of electronic PROMs (e-PROMs) enables individuals to complete assessments remotely, potentially the day or week before their appointment. Clinicians can then review the responses concurrently with the clinical notes and gain a real-time insight into the concerns that matter to patients. This needs to be considered in the development of any future PROM and successful implementation requires a trade-off between the reduction of patient completion burden versus comprehensive coverage of domains.

In order to fully appreciate PROs in clinical practice the use of PROMs need to be done in real time and hold weight in the clinical discussion about overall care. Incorporating PROMs into clinic settings, alongside other patient data, not only establishes the groundwork for shared decision-making but also empowers patients to more effectively observe improvements and changes in their condition. Additionally, it has the potential to unveil new insights into disease and treatment burden and identify needs for supportive care. However, challenges exist including constrains on time and resources, the quality of collected data may be compromised in crowded and noisy clinic environments and limitations on staff being able to support patients in completing the tools are also a concern [39, 40]. Wider validation using e-PROMs may overcome some of these logistical challenges and could facilitate global collaboration and wider patient involvement. Improvements in physician and healthcare professional engagement and education of PROMs and their outcomes are also needed, as well as consideration of factors influencing patients’ experiences of healthcare and disease management. Both PROMs and PREMs play crucial roles in enhancing the patient journey and additional efforts to examine the interplay and measurement of these outcomes should be explored.

